### Objectives

In this study, the aim is to evaluate whether using a commercially available AI tool certified for paediatric use could help HCPs make better decisions about patient care.

Primary objective:

Determine differences in diagnostic accuracy rates of HCPs for paediatric fracture detection, before and after using the AI tool.

Secondary objectives:

Determine whether differences in accuracy rates or effect of adding AI varies according to job role and experience.Determine whether user confidence in fracture diagnosis changes when using the AI tool.Determine whether management plans are altered following the use of the AI tool.

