## Methods and analysis

### Study design

The overall study design is of a cross-over multireader multicase (MRMC) study, where each reader (a HCP) will act as their own control across two imaging interpretation stages, with an interval washout period of at least 4 weeks duration (figure 1). Differences in diagnostic accuracy rates between stages, changes in reader’s confidence rates and simulated patient management will be compared. Subgroup analyses will be conducted according to reader specialty area, experience and body part interpreted.

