**Figure 1 F1:**
[figure not shown]
A diagrammatic flow chart of the multireader multicase (MRMC) study outline. AI, artificial intelligence.

At the first interpretation stage (1 September 2024–31 October 2024), each reader will review a dataset of 500 paediatric limb radiographs (some normal and some abnormal) without AI assistance, then after the washout period (1 November 2024–30 November 2024), they will proceed with the second interpretation stage (1 December 2024–31 January 2025) where they will each read the same dataset with AI assistance. The order of the radiographs, and thus imaged body parts and those with and without abnormalities, will be randomly ordered within the dataset for every reader at each interpretation stage to further reduce recall bias.

Readers will complete the imaging interpretations online, via a password-protected and secure imaging platform (details below). They will be given a 2-month period to complete the exercise and are informed not to seek help in the imaging interpretation with anyone else. Clinical information associated with each radiograph will include the age of patient and gender. Mechanism of injury, pain location, history will not be provided. The reader will be asked to assume that there is generalised pain at the joint in question, and no significant medical history (ie, no genetic or metabolic bone disorder or known malignancy).

Feedback requested from each reader for each radiograph will include:

Marking the site of a fracture on each image (or selecting ‘no fracture’).Confidence in their decision using a 5-point Likert scale (1=not confident; 5=absolutely certain).Selecting the most likely management for the patient. This will be done by providing each reader with a drop-down menu of seven predefined plans, tailored to each subspecialty, with the option for free-text comment. Examples of the different options are provided in figure 2.

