### Study cohort characteristics (imaging cases)

Cohort demographic characteristics for whole population and abnormal dataset for this study are available in online supplemental tables 1–3, with demographic data on normal dataset in online supplemental table 4. Overall, 500 different radiographic examinations across 500 different paediatric patients (none included more than once) will be used (comprising 183 fractures in 181 patients). The dataset will consist of 256 boys (97 with fractures) and 245 girls (84 with fractures), with mean age of 10 years (range 2–17 years).

The most common fractured bone in our dataset is the distal radius (41/181, 22.4% fractures), and the three the most common fracture types are Salter Harris 2 type injury (41/183, 22.4%), buckle fracture (39/183, 21.3%) and transverse fracture (28/183, 15.3%).

We will invite readers from different specialties and experience levels to participate. These will include HCPs working in radiology (including doctors and reporting radiographers), the emergency medicine department (including doctors and senior triage nurses) and orthopaedic surgeons. All experience levels will be welcome to participate, including those with a subspecialty interest within their field (eg, paediatric orthopaedic surgery, paediatric radiology). Readers will, however, be excluded if they do not routinely review paediatric radiographs as part of their expected job role.

Radiologists and reporting radiographers will be recruited voluntarily through society newsletter announcements via the European Society of Paediatric Radiology (ESPR), European Society of Skeletal Radiology (ESSR) and the British Societies of Paediatric Radiology and Skeletal Radiology (BSPR, BSSR) as well as Society of Radiographers (SoR). Emergency medical staff will be recruited through existing local collaborations, via the Royal College of Emergency Medicine (RCEM) and Association of Paediatric Emergency Medicine (APEM). Orthopaedic surgical colleagues will be recruited also via local collaborations, and via the British Society for Children’s Orthopaedic Surgery (BSCOS). All announcements and invitations to participate will be also posted via study collaborators through their personal social media channels.

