### Statistical methods/data analysis plan

The STARD-AI (Standards for Reporting of Diagnostic Accuracy - Artificial Intelligence) and CLAIM (Checklist for AI in Medical Imaging) guidelines will be adhered to in the reporting of this study.^33 34^ Diagnostic accuracy of the readers (with and without AI assistance) for each body part will be derived (ie, sensitivity, specificity, positive predictive value and negative predictive value). A true positive result will be counted if a mark made by a reader at the site of a suspected fracture falls within the area of the predefined ‘ground truth bounding box’ area set by the reference radiologists. If the mark made by a reader falls outside a bounding box, it will be counted as a false positive. Where a bounding box was set by the ground truth, but no mark made on the image then a false negative result will be assigned to the reader.

Estimates of these accuracy statistics will be derived through multilevel logistic regression models, with the reader included as a random-intercept. From these models, we will report 95% CIs, and p values (significance level set at 5%). Independent variables will be added, including the reader’s job role and experience, to assess their relationship with diagnostic accuracy. We will additionally present these same statistics to the reader, as derived through the random effects of the models, to explore the relationship between sensitivity and specificity. Intraobserver variability for the diagnostic accuracy of fracture detection before and after the use of AI assistance will also be evaluated, with subanalysis conducted to account for different reader medical specialty subgroups.

We will assess for differences in confidence scores for correctly identified images between HCPs with and without AI guidance, and also whether there were significant differences between readers across specialties and experience levels. We will also evaluate how an indeterminate AI reading affects reader decisions.

Changes in clinical management will be compared using descriptive statistics (ie, frequency and percentages) to determine, for example, how many children would be discharged with a missed fracture, or unnecessary second opinions/additional imaging sought for cases with and without AI assistance. This could provide information to help estimate potential future benefit and cost savings to the NHS at a future clinical implementation stage, where appropriate.

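### The only random effect named for the accuracy models is a reader intercept, although all readers read the same 500 examinations; accuracy CIs will be too narrow and AI-effect inference may err either way

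*Protocol article*

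**What the plan says.** The Study design section calls this a "cross-over multireader multicase (MRMC) study, where each reader (a HCP) will act as their own control across two imaging interpretation stages". In stage 1, "each reader will review a dataset of 500 paediatric limb radiographs (some normal and some abnormal) without AI assistance"; in stage 2, "they will each read the same dataset with AI assistance". The section on study cohort characteristics gives "500 different radiographic examinations across 500 different paediatric patients (none included more than once) will be used (comprising 183 fractures in 181 patients", which leaves 500 - 181 = 319 normal examinations. At least 40 readers are expected.

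The primary objective is to "Determine differences in diagnostic accuracy rates of HCPs for paediatric fracture detection, before and after using the AI tool". For the inference, the section Statistical methods/data analysis plan says: "Estimates of these accuracy statistics will be derived through multilevel logistic regression models, with the reader included as a random-intercept". The 95% CIs and the p values, at a 5% significance level, come from these models. The additions it names are independent variables, including job role and experience. Reader-level statistics are to be reported "as derived through the random effects of the models". Accuracy is to be derived for each body part. The article mentions no random effect for the examination, no reader-by-AI or examination-by-AI term, and no MRMC or two-way variance.

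**The concern.** With 40 readers, the 181 abnormal examinations produce 40 x 181 = 7,240 reads per stage. A subtle fracture tends to be missed by many readers together, so these reads are not 7,240 independent pieces of information, even after allowing for how good each reader is. A model with a reader intercept alone assumes that they are.

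The protocol itself gives reasons to expect the omitted variation. Its Introduction describes some paediatric injuries as hard to see. The case set mixes fracture types and includes normal variants. Under Intervention (AI tool), the software gives a single output per image, so in stage 2 a wrong output reaches every reader at once. The secondary objectives ask whether the AI effect differs by role and experience.

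At stake are the error bars on every sensitivity and specificity reported, and the p value for the primary comparison.

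**Working it through.** **The plan's own figure.** No stated figure bears directly on CI calibration. The nearest is the minimum of 112 examinations with 10 readers per body part. It cannot be reproduced, because baseline AUC, reader variability and correlations are not given. Over assumed ranges the required number runs from 54 to over 1,000, and AUC 0.90 with small reader variability gives 110-113. The figure is therefore not shown to be wrong, and nothing below depends on it.

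**Inputs from the protocol.** 40 readers; 181 abnormal and 319 normal examinations; 44 to 46 abnormal per body part (45 used); two stages; alpha 5%, taken as two-sided.

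**Assumed inputs (not in the protocol).** SDs on the logit scale: reader 0.5; case 0, 1 or 2; case-by-AI 0, 0.5, 1 or 1.5; reader-by-AI 0 or 0.3. True sensitivity was 0.755 to 0.806 and true specificity 0.824 to 0.891, with no true AI effect.

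**Models.** For reader i, examination j and stage k:
- Data generated from: logit p = mu + beta x AI(k) + reader(i) + case(j) + reader-by-AI(i,k) + case-by-AI(j,k), with beta = 0.
- Planned model, read as one model with both stages stacked: logit p = mu + beta x AI(k) + reader(i).
- Comparison: two-way variance (MS_reader + MS_case - MS_residual)/(J x n), with J readers and n examinations.

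There were 500 runs per scenario, so the Monte Carlo SE is about 1 point near 5% (sqrt(0.05 x 0.95/500) = 0.0097) and about 2 points near 25% or 50%.

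**Results for the planned model.** Ratio = true SD / model SE.

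| Case SD | Case-by-AI SD | Reader-by-AI SD | Sensitivity, n=181: ratio, coverage | Sensitivity, n=45: ratio, coverage | AI effect, n=181: ratio, type I | AI effect, n=45: ratio, type I |
|---|---|---|---|---|---|---|
| 0 | 0 | 0 | 1.04, 92.0% | 1.03, 93.4% | 1.03, 6.6% | 0.98, 4.2% |
| 1 | 0 | 0 | 1.32, 85.6% | 1.85, 70.2% | 0.96, 4.4% | 0.91, 2.4% |
| 2 | 0 | 0 | 2.06, 64.0% | 3.06, 48.8% | 0.80, 1.4% | 0.82, 1.2% |
| 1 | 0.5 | 0 | 1.36, 82.8% | 1.93, 69.0% | 1.24, 11.4% | 1.29, 12.4% |
| 2 | 0.5 | 0 | 2.08, 65.0% | 3.11, 48.4% | 1.06, 7.2% | 1.09, 6.8% |
| 1 | 1 | 0 | 1.47, 80.4% | 2.13, 64.0% | 1.85, 27.0% | 1.90, 30.0% |
| 2 | 1 | 0 | 2.16, 63.0% | 3.20, 44.8% | 1.60, 20.8% | 1.62, 23.2% |
| 2 | 1.5 | 0 | 2.27, 60.4% | 3.35, 40.8% | 2.19, 36.8% | 2.21, 37.2% |
| 0 | 0 | 0.3 | 1.07, 93.0% | 1.07, 92.0% | 1.47, 17.8% | 1.12, 6.8% |

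For specificity (n=319) with case SD 1 to 2, coverage was 67-89%.

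**Hand check.** For a normal estimate, coverage = 2 x Phi(1.96/ratio) - 1.
- Ratio 2.06: 1.96/2.06 = 0.951, giving 66% (simulated 64.0%).
- Ratio 3.06: 1.96/3.06 = 0.641, giving 48% (simulated 48.8%).

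Type I error = 2 x (1 - Phi(1.96/ratio)).
- Ratio 0.80: 1.96/0.80 = 2.45, giving 1.4% (simulated 1.4%).
- Ratio 1.85: 1.96/1.85 = 1.059, giving 29% (simulated 27.0%).

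**In percentage points.** For one body part with case SD 2 and no AI interaction, the model SE is 0.0124 and the true SD 0.0381. The reported half-width would be 1.96 x 0.0124 = 2.4 points, where 1.96 x 0.0381 = 7.5 points is needed.

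**Reading the table.** The first row shows that the planned model behaves almost as intended when cases do not differ. Case difficulty alone spoils the accuracy CIs. For the AI contrast, difficulty is shared by both stages and cancels, so the model SE is then too large; case-by-AI or reader-by-AI variation does not cancel and makes it too small. The two-way variance gave 93-96% coverage and 3-7% type I error in all scenarios. A separate simulation with case SD 1.5 agreed: coverage about 67-74% (181 fractures) and 49-60% (45 fractures), and type I error from about 1% to about 30%.

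**The case against.** The strongest defence is that this is a condensed article and the analysis plan is not shown. The text does not say that the reader is the sole random effect, it later speaks of random effects in the plural, and it never labels a primary model. This has some weight, but the article does more than stay silent: it names the clustering unit and ties the CIs and p values to it. As written, that structure does not match the design. It is also the only inferential model given for the primary objective.

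Second, inference conditional on these 500 selected examinations is legitimate, if narrower. The article does not state that target, so this is a partial defence.

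Third, several stronger readings are tempting but not supported:
- A reader might infer that the AI p values are bound to be too small. They are not: with case differences alone the test is conservative, and the document gives no variances that would settle the direction.
- A reader might infer that the reader-level results cannot show who gains from AI. That presumes one stacked model with a common AI term, which the article does not specify. Models fitted by stage would give each reader an intercept per stage, and the planned role and experience terms could absorb some of the variation in benefit.
- Pooled type I error is not due to cases alone: reader-by-AI SD 0.3 by itself gives 17.8% for sensitivity and 21.2% for specificity, but only 6.8% per body part.

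**Conclusion.** The point stands in two parts of unequal strength. For sensitivity and specificity, CIs from a reader-intercept model are too narrow whenever examinations differ in difficulty. This held in every scenario with case variance, and by the same mechanism it applies if the stages are modelled separately. It is worst per body part, the level at which the article says accuracy is derived. Confidence here is high.

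For the AI effect, inference from a stacked model is miscalibrated in a direction that depends on unknown variances: type I error about 1-4% with a case main effect only, 7-12% with case-by-AI SD 0.5, 21-30% with SD 1 and about 37% with SD 1.5. A case-by-AI effect is plausible because all readers see the same output, but its size is an assumption. All magnitudes rest on the assumed variance components. The structure should be corrected before the analysis is run.

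**What to change.** In the section Statistical methods/data analysis plan, replace the reader-only random intercept with crossed random effects for reader and examination, and add reader-by-AI and examination-by-AI terms where they can be estimated. State in advance that if the model does not converge, which is a real possibility with 44 to 46 abnormal examinations per body part, the CIs and p values will come from an MRMC variance (Obuchowski-Rockette) or a two-way bootstrap over readers and cases. A joint model for abnormal and normal examinations is optional and not needed to cure this defect.

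The cost is a change of wording and more computing time, with no new reads. Intervals for sensitivity and specificity will usually be wider; the interval for the AI effect may widen or narrow.

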**Trial registration number:**

ISRCTN12921105.

STRENGTHS AND LIMITATIONS OF THIS STUDYPerforming a large multireader study evaluating paediatric fracture detection with and without artificial intelligence (AI) assistance across different medical subspecialties and experience levels will better evaluate which healthcare professionals benefit most from AI assistance.Our imaging dataset represents a range of children’s ages and body parts across multiple National Health Service trusts to comprehensively evaluate performance of a commercially available AI algorithm.The UK-based population used in this study, lack of patient history with predefined simulated clinical management choices may not exactly mimic real-world practices and outcomes.Replicating societal and ethical biases, with a comprehensive health economic evaluation of providing AI assistance for fracture detection is difficult to achieve, but our study will provide a guide for future studies.

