We anticipate a minimum of 40 readers (approximately 14 readers from each specialty) equally split between trainees and consultant-level experience. Each reader will be provided instructions on how to participate in the study and complete a consent form online asking about their demographic details, job role/specialty and experience level. Prior to any interpretation, a short video and instruction sheet on how to use the online reporting platform will be provided. Reporters will be asked to replicate their usual reporting practices as far as possible (eg, use of a suitable monitor, dim lighting) and would be able to use reference tools (eg, textbooks or websites) that they would normally consult for this task, but just not to consult other reporters.

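### The analysis states no comparison of the AI effect between reader groups, although secondary objective 1 asks for one, and the reader random intercept it specifies would understate the error of such a comparison

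*Protocol article*

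**What the plan says.** **The question.** The Objectives section lists as the first secondary objective: "Determine whether differences in accuracy rates or effect of adding AI varies according to job role and experience". This has two parts: whether accuracy differs between kinds of reader, and whether the AI effect does. The list of strengths promotes the second part, saying that the study "will better evaluate which healthcare professionals benefit most from AI assistance".

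**The analysis.** The statistical methods section fixes the model: "Estimates of these accuracy statistics will be derived through multilevel logistic regression models, with the reader included as a random-intercept". It continues that further variables will be added, among them the reader's "job role and experience, to assess their relationship with diagnostic accuracy". The Study design section says "Subgroup analyses will be conducted according to reader specialty area, experience and body part interpreted". The statistical section also plans an analysis of intraobserver variability before and after AI, "with subanalysis conducted to account for different reader medical specialty subgroups"; experience is not mentioned there. Confidence scores are compared across specialties and experience levels, but that is a different outcome.

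**The concern.** The purpose given for adding role and experience matches only the first part of the objective. If they enter as main effects, the model fits one AI odds ratio shared by every role and grade, so it cannot show who gains more. Subgroup analyses would describe the gain within each group, but a set of within-group results is not a comparison between groups.

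The second difficulty is the error term. The AI effect is measured within a reader, while role and experience vary between readers. Whether trainees gain more than consultants is therefore a comparison of two sets of reader-level gains, and its uncertainty must include how much gains differ among readers of the same kind. A random intercept carries only differences in the readers' general level of accuracy. At stake is the answer to a named secondary objective that the article presents as a strength; the primary objective is not the subject of this point.

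**Working it through.** The plan gives no figure for this comparison, so there is none to reproduce.

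**Inputs from the protocol.** "We anticipate a minimum of 40 readers (approximately 14 readers from each specialty) equally split between trainees and consultant-level experience", hence 20 against 20 for experience; 181 abnormal cases; 5% significance level.

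**Assumed, because the protocol gives none.** Baseline sensitivity 70% to 90%; AI effect 0.4 to 0.8 on the log-odds scale; between-reader SD of that effect (s) of 0, 0.3 or 0.5.

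**1. What main effects can show.** Take an AI odds ratio of 2.0 in trainees and 1.0 in consultants, with baseline log-odds of 1.0 and 1.6. Fitted to the expected data, a logistic model with main effects of AI and experience returns one AI odds ratio of 1.45 for everyone. Adding the AI-by-experience term recovers 2.0 for trainees and an interaction odds ratio of 0.50.

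**2. Type I error when variation in gain is left out.** The sampling variance of one reader's log odds ratio is about v = 1/[181·p0(1−p0)] + 1/[181·p1(1−p1)]. The true variance of a reader's gain is v + s². A test using v alone has type I error of about 2·[1 − Φ(1.96/√(1 + s²/v))].

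- p0 = 0.70, effect 0.4, so p1 = 0.777: v = 0.026 + 0.032 = 0.058. With s = 0.3, √(1 + 0.09/0.058) = 1.60 and the error is 22%. With s = 0.5 the ratio is 2.30 and the error is 39%.
- p0 = 0.90, effect 0.8, so p1 = 0.952: v = 0.061 + 0.122 = 0.183. With s = 0.3 the ratio is 1.22 and the error is 11%. With s = 0.5 the ratio is 1.54 and the error is 20%.
- s = 0: the ratio is 1 and the error is 5%.

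Simulation over the same settings, pooling reader log odds ratios by inverse variance with no true interaction, agrees to within a few points:

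| SD of AI gain (assumed) | Variation in gain ignored | Reader-level comparison |
|---|---|---|
| 0 | about 5% | about 5% |
| 0.3 | 10–20% | 4–6% |
| 0.5 | 22–37% | 4–6% |

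Both calculations stand in for the multilevel model rather than fit it, and neither includes variation between cases.

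**3. Subgroup significance as a substitute.** If three specialties have the same true gain and each test has power p, independent tests disagree on significance with probability 1 − p³ − (1−p)³. This is 75% at p = 0.5, 48% at p = 0.8 and 3% at p = 0.99. The protocol gives no power per specialty, so the figure may be large or negligible. All readers also see the same cases, which would tend to make the tests agree more often.

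**4. Power of the interaction.** If the overall AI effect had 80% power, its standardised size is 1.96 + 0.84 = 2.80. A difference of that same magnitude between two equal groups has twice the standard error, hence 1.40, and power Φ(1.40 − 1.96) = 29%. At 90% overall power it is Φ(3.24/2 − 1.96) = 37%.

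**The case against.** The strongest reply is that this is an omission in a condensed article. Interaction terms and random slopes are ordinary content of a statistical analysis plan, which is not shown. The objective is correctly worded, subgroup analyses are promised, and readers' experience and subspecialty are kept so that groups can be compared. The list of added variables is open.

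Much of this stands, and it rules out stronger readings that a reader might infer:

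- *That differential AI benefit will not be tested.* The text supports only that no such test is stated. It nowhere says that role and experience will enter solely as main effects.
- *That each subgroup will get its own p value, and that benefit will be claimed where one is significant and another is not.* The Study design section says only that subgroup analyses will be done. It names neither separate models nor a rule of inference, and the strengths item expresses an aim.
- *That subgroups with equal benefit would usually disagree on significance.* This depends wholly on an assumed power per specialty, as step 3 shows.

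The reply does not dispose of the point. The article goes beyond silence: it fixes the random-effects structure and says what the added variables are for, and these do not fit the second half of its own objective. An unseen plan that added the interaction to the stated random-intercept model would still have the wrong error term whenever readers differ in gain.

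**Conclusion.** The point holds as a mismatch between secondary objective 1 and the analysis described for it. The stated purpose of the covariates addresses accuracy by role and experience; no comparison of AI gain between groups is stated; and the specified reader random intercept is not an adequate error term for one.

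The size is conditional. Type I error is roughly 10% to 37% instead of 5% for assumed SDs of gain of 0.3 to 0.5 on the logit scale, baseline sensitivity of 70% to 90% and 20 against 20 readers. It is 5% if all readers gain equally. The direction does not depend on the particular values: any real variation in gain makes the p value too small. The documents do not establish that the comparison will be left untested or drawn from subgroup p values.

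**What to change.** State that the second part of secondary objective 1 is assessed by AI-by-specialty and AI-by-experience terms in the sensitivity and specificity models, with a random AI slope for each reader, or by an equivalent comparison of reader-level gains. Report differences in AI gain between groups with 95% CIs and an interaction p value for each factor. Say that differential benefit will not be inferred from one subgroup being significant and another not; whether to print within-subgroup p values as well is a matter of preference.

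Label these results secondary. The sample size section is based on an AUC difference of 0.05 between reader and AI algorithm, not on this contrast.

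The cost is analysis wording only, with no new readers, cases or data items. The price is wider intervals than the random-intercept model would give and limited power for the interaction (step 4), so the CIs should carry the interpretation and a non-significant interaction should not be read as equal benefit.

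### With one unaided and one aided reading per reader and case, test-retest intraobserver variability cannot be estimated, and the management objective is given percentages with no measure of uncertainty

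*Protocol article*

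**What the plan says.** All references are to the protocol article.

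- **Design.** Under Study design, "each reader (a HCP) will act as their own control across two imaging interpretation stages". In the text after Figure 1, at the first stage "each reader will review a dataset of 500 paediatric limb radiographs (some normal and some abnormal) without AI assistance"; after the washout, "they will each read the same dataset with AI assistance". The order of conditions is the same for everyone. Only the order of the radiographs is randomised.
- **Cases.** Under Study cohort characteristics, "500 different radiographic examinations across 500 different paediatric patients (none included more than once) will be used".
- **Variability analysis.** Under Statistical methods/data analysis plan, "Intraobserver variability for the diagnostic accuracy of fracture detection before and after the use of AI assistance will also be evaluated", with a subanalysis by reader specialty.
- **Management.** A secondary objective is to "Determine whether management plans are altered following the use of the AI tool". The analysis section states "Changes in clinical management will be compared using descriptive statistics (ie, frequency and percentages". Its examples are "how many children would be discharged with a missed fracture, or unnecessary second opinions/additional imaging sought for cases with and without AI assistance". The abstract also describes this analysis as descriptive.
- **Uncertainty.** The same section attaches 95% CIs and p values to the accuracy models, which have a random intercept for reader. It attaches none to management.

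**The concern.** Intraobserver variability normally means the disagreement of one reader with himself or herself on the same case under the same condition. The wording promises this before and after AI, but the design has no repeat reading in either condition. If the two stages are compared and the result carries that name, a tool that corrects many missed fractures lowers the agreement, and the report would read as reader inconsistency. Part of what looks like an AI effect would also be ordinary re-reading noise.

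For management, the objective asks a yes-or-no question, while the stated method gives percentages alone. The readings are clustered by reader and by case. A reader of the report could not judge from raw percentages whether a difference between stages exceeds chance, and the article suggests that these results could inform later estimates of benefit and cost savings.

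**Working it through.** **1. Readings available per reader, case and condition**

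Inputs: 500 cases, none repeated; two stages, one per condition; a minimum of 40 readers.

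- Readings per reader, case and condition = 1.
- Same-condition pairs per reader and case = 0, overall and in every specialty.
- Unaided-aided pairs = 40 × 500 = 20,000. With fractures in 181 patients, these are 40 × 181 = 7,240 on abnormal and 40 × 319 = 12,760 on normal examinations.

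**2. Why agreement between stages cannot be split into noise and AI effect**

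Take an illustrative paired table with 15% wrong-to-right and 5% right-to-wrong. Write each observed direction as noise plus AI effect.

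| | Noise each way | AI up | AI down | Observed up | Observed down | Gross | Net |
|---|---|---|---|---|---|---|---|
| A | 0% | 15% | 5% | 15% | 5% | 20% | +10 points |
| B | 5% | 10% | 0% | 15% | 5% | 20% | +10 points |

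Agreement is 100% − 20% = 80% in both. True re-reading disagreement is 0% in A and 5% + 5% = 10% in B. The data cannot tell these apart. Any period effect adds a third component, since AI is always second.

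**3. What noise does to gross and net change when AI does nothing**

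The document gives no re-reading rate, so the following are assumptions: sensitivity 0.75, and detection probabilities from a beta distribution with parameters 0.75c and 0.25c, where c runs from 0.5 to 4. With two independent readings:

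- Gross switching = 2 × 0.75 × 0.25 × c/(c + 1) = 0.375 c/(c + 1). This is 0.125 at c = 0.5 and 0.30 at c = 4.
- Share of stage 1 misses found at stage 2 = (gross/2)/0.25. This is 0.25 at c = 0.5 and 0.60 at c = 4.
- Expected net change = 0.

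A simulation of 40 readers × 181 fracture cases with 2,000 replicates agreed: gross switching 12.5% to 30%, 25% to 60% of misses found at stage 2, and mean net change in sensitivity about 0.000. Re-reading noise thus inflates switch counts but cancels in expectation in totals per condition.

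**4. Why the management percentages need an interval that allows for clustering**

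Write the variance of the paired difference for one reading as reader + case + residual parts, none negative and summing to 1. For abnormal examinations, the variance of the mean net difference is

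reader/40 + case/181 + residual/7,240.

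Treating all pairs as independent gives 1/7,240. The ratio of true to naive standard error is then:

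- all residual: 1
- all case: √(7,240/181) = √40 = 6.3
- all reader: √(7,240/40) = √181 = 13.5

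The document gives no variance components, so the ratio can lie anywhere from 1 to 13.5. The size of the denominators therefore says little about precision.

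**The case against.** **The term may mean change between stages.** Each reader is his or her own control, so the sentence can be taken as within-reader change or agreement between unaided and aided readings. That is estimable, and the choice of statistic can be left to the SAP. This stands in part: a reader might infer that nothing within readers can be estimated, and that goes too far. On this meaning the fault is one of label and interpretation, but the sentence still needs changing, because the two-stage quantity is not intraobserver variability before or after anything.

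**Agreement will not be read alone.** Sensitivity, specificity and predictive values will be reported with and without AI. This stands, and it limits the harm.

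**Management totals are not distorted by re-reading noise.** A reader might infer that the plan counts every changed management plan as an AI effect. The document does not say so. Its examples are totals with and without AI, in which symmetric noise cancels in expectation. The noise argument therefore holds only for case-by-case switch counts, which the article does not specify, and no count of spurious management changes should be held against it.

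**Descriptive reporting is a declared choice for a secondary objective, and intervals are SAP detail.** This has some weight. But the article does not leave the method open: it defines it as frequencies and percentages, for an objective phrased as a determination.

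**Conclusion.** The point holds as a design-analysis mismatch in secondary analyses. There are zero same-condition pairs, so test-retest intraobserver variability cannot be estimated in either condition or in any specialty; this needs no assumption beyond the stated design. The quantity that can be estimated, within-reader agreement between conditions, combines noise, AI effect and period effect, and would mislead under its present name.

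For management, the defect is the missing uncertainty for a stated objective, not bias from re-reading noise. Its size cannot be fixed from the document. The standard-error ratio of 1 to 13.5 is a bound under an additive reader-and-case model, and the rates in the no-effect simulation rest on assumed sensitivity and heterogeneity. The primary comparison of accuracy is outside this point.

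**What to change.** In Statistical methods/data analysis plan:

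1. Replace the term intraobserver variability with *within-reader agreement between the unaided and aided readings*, overall and by specialty.
2. Show both directions of change, wrong-to-right and right-to-wrong. State that gross switches contain re-reading noise and any period effect and are not attributed to AI. Between-reader variability at each stage may be added, as a separate question.
3. For management, keep the frequencies and percentages. Add the net paired difference (with minus without AI) and a 95% CI that allows for clustering by both reader and case, for the two outcomes already named: discharge with a missed fracture (abnormal examinations) and unnecessary second opinion or additional imaging (normal examinations).

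Cost: no new readings and slightly more analysis work. The management model needs a case effect, which the article's reader-only random intercept for accuracy lacks. The net difference removes symmetric noise in expectation but not a period effect from the fixed order, and the report should say so. If true test-retest variability is wanted, it needs a subset re-read in the same condition, at the cost of extra reader time.
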